## Methods

### Design

We chose a type 2 hybrid effectiveness-implementation design to evaluate the effectiveness of the clinical interventions and the implementation strategies.^20–23^ Mixed methods will be used as the method of evaluation. DR care pathway was developed by the Kerala Health Secretary, non-communicable diseases lead, Health and Medical Education service providers, technical and EHR teams, local authorities and the GCRF/UKRI-funded coapplicants from the UK. The DR care pathway will be set-up in a staggered approach with five FHCs initiated in the first 3 months and the remaining 11 centres will be added based on acceptance of all stakeholders and adapting and training phase for 12 months from 15 March 2018. A further 12–15 months will be allocated to recruit consenting patients to a cross-sectional study to gather quantitative data for the effectiveness outcomes. A minimal data set from this study will also be entered into EHR to enable future screening for the consented patients. Qualitative data collection from interviews of staff, patients and focus groups at baseline and end of study and all field notes gathered during the study will be utilised to inform evaluation of the implementation strategy.^20–22^

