### Description of the standard of care

Currently, patients with diabetes are not systematically screened for DR in the public health system. Most patients present to the tertiary centre voluntarily either because of increased awareness of complications of diabetes or due to visual impairment. Therefore, the current standard of care will be captured as the number of patients presenting to the tertiary centre for an eye consultation for DR over a period of time as there is no baseline data in the primary and secondary care. This cross-sectional survey of the patients presenting at the FHCs will provide information on the uptake of screening of people registered in the non-communicable diseases register at the start of the study. The prevalence of DR and STDR of the screened population will be estimated from the numbers screened in all the non-communicable diseases registers during this period.

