### Outcomes

Prespecified outcomes of the effectiveness of the DR pathway and the evaluation of the implementation strategy are tabulated in tables 2 and 3, respectively.

**Table 2 T2:** DR pathway (intervention)-related outcomes

Outcomes	Indicators	Source of data
Clinical effectiveness	Proportion of people screened for DR in each family health centres over 12 months. Proportion of referred patients with STDR. Proportion of ungradable retinal images and percentage of cataract identified from referring these patients. Risk and complication burden in people screened for DR Presenting visual acuity of those referred from the DR pathway compared with those who self-referred to secondary care. Generalisability of the prevalence data compared with house-to-house survey in a neighbouring district.	Data from monthly entries into EHR and study database. −
Safety	Data on complications of the DR pathway	EHR and study database
Cost-effectiveness	The key outcome is the number of cases of severe visual impairment or blindness due to STDR averted as a result of the new DR care pathway and resultant QALY gain. Estimated QALY gain from laser treatment of STDR and from cataract surgery, using utility values from Rachapelle *et al*.^32^ Assumption that the effect of no screening is as in historic studies that reported the rate at which STDR leads to blindness if left untreated.	Data collected in the study, data from the literature and expert opinion where data could not be collected.
Efficiency	Efficiency is defined as optimal use of the service. For this purpose, we will first estimate the time required to process one patient from the path-process analysis. This estimate will be used to determine the number of patients who can be seen on a day. We will then calculate (1−number of patients screened)/number of patients who can be screened). Proportion can be used in a p-type control chart.^33^	Capture efficiencies in structures, resources and processes across the DR care pathway from staff interviews. Path-process mining of patients screened in family health centres analysis will be based on detailed time-event logs of approximately 70 patients from the 16 FHCs
Patient satisfaction	Patients willingness to be screened and their satisfaction with the information provided to them and the care they received	Patient interviews and telephone survey of patients referred to secondary care for treatment

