Timeliness	Path-process mapping at family health centres to understand delays in pathway Reasons for non-attendance for those referred to secondary care for treatment of STDR	Path-process mapping at family health centres to understand delays in DR care pathway Patient survey and secondary care records
Equity	Age and gender-based prevalence of DR and STDR will be reported on consented patients from all family health centres. Reasons of non-referral of patients that require referrals will be recorded. Numbers denied screening despite willingness to be screened will also be reported.	Data from EHR and study database.

DR, diabetic retinopathy; EHR, electronic health records; FHCs, family health centres; QALY, quality-adjusted life year; STDR, sight-threatening diabetic retinopathy.

**Table 3 T3:** Outcomes of the evaluation of the implementation strategy

Outcomes	Indicators	Assessment and data source
Acceptability	Willingness of each family health centres to be involved in the DR care pathway. Staff willingness to train patients acceptability of the pathway.	*Assessment:* Readiness to implement the DR care pathway in the 16 family health centres and any reasons for delay. *Data source:* Clinical performance from family health centres that will include monthly uptake of DR screening at each centre and any reports on barriers causing delays in implementation provided by the project manager. *Assessment:* Proportions of trained ASHAs, nurses and doctors per family health centres, increase in doctors trained in laser surgery in secondary care, proportions willing to be included in train the trainer programme. The denominator will be total numbers of each personnel available to be trained on the date of implementation. *Data sources:* Accreditation and certification records; structured interviews of at least 5 nurses and 5 primary care doctors from 16 family health centres, 3–5 ophthalmologists from secondary and tertiary care, 2 data entry operators and 5 ASHAs and 1 health service administrator to understand challenges for acceptance. *Assessment:* Screening attendances per family health centres over 12 months. *Data sources:* Clinical performance data and a telephone questionnaire survey for screened and referred patients to evaluate reasons for attendance and non-attendance.

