### Statistical analyses

We will create a complete case data set of the cross-sectional survey for use in the analyses of effectiveness and assess the potential impact of missing data using sensitivity analysis incorporating a range of optimistic and pessimistic scenarios for the impact of missing data. We will model two outcomes that we hypothesised would be influenced by the intervention: (1) uptake of DR screening (primary outcome) and (2) numbers of patients referred for STDR as a result of screening. We will use bivariate logistic regression models to assess crude associations between sociodemographic factors such as age, gender, education, income and living arrangements, and other clinical data with DR and STDR and use fractional polynomials to account for the form of continuous covariates to predict uptake of DR screening. Factors associated with a p<0.25 will be candidates for inclusion in the multivariable logistic regression models. We will test interactions among identified main effects to capture improvement in model prediction assessed by reduced residual variance-based statistics. To account for the staggered entry into the study, we will add a variable indicating the month of entry of each FHCs into the programme (eg, 1. if the FHC join in the first month of the programme, 2. if in the second month and so on). A non-significant coefficient for this variable will suggest the staggered approach had no effect and a significant coefficient will allow the effect to be quantified for each FHC. In our final adjusted model, we will consider associations with a p<0.05 as statistically significant. Adequacy of model discrimination and calibration will be assessed using receiver operating characteristic curves. The validation of the telemedicine will be reported as the agreement (kappa statistics) between screen positive patients graded by the graders at the reading centre versus the DR grade as recorded by the ophthalmologists in secondary care centres. A kappa coefficient of 0.6 or higher was prespecified to indicate validity.

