One of the strengths of this study is that quantitative data backed by qualitative data will be collected to strengthen our findings and enable generalisation of our findings. Second, we will use robust statistical methods to reduce bias including selection bias and other confounders. Finally, the access to and collaboration with the UK is a key strength of the study, as it facilitates the codevelopment of the interventions from the outset. Active involvement of policy makers engaged in transformation of primary care to screen for and address complications of non-communicable diseases who value research to generate evidence for policy making and who are prepared to learn from, and adapt the DR care pathway based on implementation experience is a unique feature of this study. Findings on the mechanisms and contexts that optimise the implementation of this complex multifaceted intervention using the ERIC taxonomy will be useful to those developing and implementing these programmes in other health systems. The health economic model may highlight the health expenditure required at individual, family and Kerala State level for forecasting and planning health budgets.

Perhaps the most important aspect of the chosen evaluation is that it is built within a simultaneous developing public health strategy on population-based screening of diabetes and hypertension and a recently introduced EHR called eHealth. Conducting research in such an environment is a good example of health policy and systems research.

Despite the limitations, this study holds promise for providing high-quality data and detailed implementation information on a complex intervention in a resources-limited setting. We hope to contribute to the literature on the implementation and effectiveness of DR screening and treatment in the public health sector in LMICs.

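### Selection-bias reduction is claimed as a strength, but no stated analysis corrects DR and STDR prevalence for who attended

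*Protocol article*

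**What the plan says.** In the Discussion of the protocol article, the second listed strength is that "we will use robust statistical methods to reduce bias including selection bias and other confounders". No method is named there.

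Prevalence is described in three places:

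- Description of the standard of care: "The prevalence of DR and STDR of the screened population will be estimated from the numbers screened". The source is people who come to the family health centres (FHCs): "This cross-sectional survey of the patients presenting at the FHCs will provide information on the uptake of screening".
- Design: entry also requires consent. "A further 12–15 months will be allocated to recruit consenting patients to a cross-sectional study".
- Outcomes, Table 2, equity row: "Age and gender-based prevalence of DR and STDR will be reported on consented patients from all family health centres".

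Table 2 also lists, under clinical effectiveness, "Generalisability of the prevalence data compared with house-to-house survey in a neighbouring district". So prevalence is meant to be read beyond the people screened.

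On analysis, the Statistical analyses section begins with "We will create a complete case data set of the cross-sectional survey for use in the analyses of effectiveness". It adds optimistic and pessimistic missing-data scenarios, logistic models for DR and STDR, a model that predicts screening uptake, a variable for each centre's month of entry, ROC curves, and kappa for grading agreement.

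**The concern.** People who attend for screening may differ from the rest of the register in ways that also drive retinopathy, such as age, diabetes duration and visual symptoms. The article itself says, for the tertiary centre, that patients now come mostly because they are aware of complications or already have visual impairment. If attendance at the FHCs follows a similar pattern, prevalence among attenders differs from prevalence in the register. The reverse is also possible, since long-standing or frail patients may attend less.

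A reader of the Discussion would take it that the analysis deals with this. If it does not, two uses are exposed: any statement of how much DR or STDR exists in the register, and the comparison with a house-to-house survey, which does not depend on people coming to a clinic.

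**Working it through.** **Step 1. The claim against the stated methods.**

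- Complete-case set and missing-data scenarios: these concern missing data in the survey. The text does not extend them to people who never attended.
- Logistic models for DR and STDR: these describe associations among people screened.
- Uptake model: describes who attends, but is not linked to the prevalence estimate.
- Month-of-entry variable: addresses the staggered start.
- ROC curves and kappa: model performance and grading agreement.
- House-to-house comparison: an external check. A difference would mix selection with true differences between districts.
- Age- and gender-specific prevalence: the raw material for standardisation, but reported for consented patients only.

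Some of these examine selection. None is stated as a correction of prevalence.

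**Step 2. Possible size.** The documents give no uptake by patient characteristic, so the inputs below are assumptions, apart from the expected 8% DR and 3% STDR in the Sample size section. Assume one third of the register has long-duration diabetes, with DR 12% against 6% and STDR 6% against 1.5%. The register values then match the protocol:

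- DR = 1/3 × 12% + 2/3 × 6% = 8%
- STDR = 1/3 × 6% + 2/3 × 1.5% = 3%

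Share of long duration among the screened = (1/3 × u1) / (1/3 × u1 + 2/3 × u2), where u1 and u2 are uptake in the long-duration group and in the rest.

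| u1 / u2 | Long-duration share | Observed DR | Observed STDR |
|---|---|---|---|
| 30% / 10% | 60% | 9.6% | 4.2% |
| 20% / 10% | 50% | 9.0% | 3.75% |
| 10% / 20% | 20% | 7.2% | 2.4% |

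For the first row, STDR = 0.6 × 6% + 0.4 × 1.5% = 4.2%. Reweighting the two strata to their register shares returns 8% and 3% in every row, provided that attendance within a stratum is unrelated to DR.

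A more general form uses r, the attendance ratio of people with the condition to people without: observed = r·p / (r·p + 1 − p). For an assumed r of 0.5 to 2, a true 8% is seen as 4.2% to 14.8%, and a true 3% as 1.5% to 5.8%.

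**Step 3. Against sampling error.** The protocol's final size reproduces as 377 × 3 = 1131. With its design effect of 3, the 95% half-width is 1.96 × √(3 × p(1 − p)/1131):

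- DR at 8%: 2.7 points
- STDR at 3%: 1.7 points

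The biases in the table (at most 1.6 points for DR and 1.2 for STDR) lie inside these half-widths. At the ends of the wider range the biases are 3.8 to 6.8 points for DR and 1.5 to 2.8 for STDR, mostly outside them. A confidence interval does not reveal such a bias, and screening more people does not remove it.

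**Step 4. Which figure serves which use.** Take the 40 000 people with diabetes assumed in the Sample size section and uptake of 30% / 10%:

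- Long duration: 13 333 × 0.30 = 4000 screened, × 6% = 240 STDR
- Rest: 26 667 × 0.10 = 2667 screened, × 1.5% = 40 STDR
- Total: 280 of 6667 = 4.2%, the observed prevalence

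Applying the standardised 3% to the 6667 screened gives 200, which understates the screening yield by 80/280 = 29%. For burden in the whole register the position is reversed: 40 000 × 3% = 1200 is correct, and 40 000 × 4.2% = 1680 is not.

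**The case against.** The strongest objection is that the stated target is the screened population, and for that target attendance is not a bias. This stands. It also stands that workload follows from uptake times observed prevalence, as Step 4 shows. A reader might infer that a standardised figure should replace the observed one in scale-up planning; for workload, that would introduce an error.

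Other stronger readings also fail:

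- That nothing in the plan touches selection. The uptake model and the survey comparison do examine it.
- That the article specifies an unweighted estimate. It is silent on weights, and a full analysis plan that is not shown might add them.
- That the register is known to hold what weighting needs. The Quantitative data section takes age, gender and duration from the electronic record but does not say they exist for non-attenders. Table 1 has operators entering full data in the clinics, which suggests that detailed fields may be filled mainly for attenders.
- That prevalence is known to be overstated. The scenarios run both ways.

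It can also be said that the choice of weights belongs in an analysis plan, and that the Discussion openly admits measured and unmeasured biases in a study without controls. Both are fair. What remains is an affirmative claim of bias reduction that the article's own methods do not support, together with an intention to test how far prevalence generalises.

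**Conclusion.** The point holds in a limited form. The Discussion claims statistical reduction of selection bias, while the stated analyses describe or examine attendance and do not correct DR or STDR prevalence for it. Observed prevalence is sound for the screened population and, multiplied by uptake, for screening and referral workload. It may be biased in either direction as an estimate of register burden or in the comparison with a population survey.

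The size is not known. On the two-group assumptions, a register STDR of 3% would be seen as 2.4% to 4.2%, and a DR of 8% as 7.2% to 9.6%. These ranges rest on assumed stratum sizes, risks and uptakes. The primary outcome, the proportion of the register screened, is not affected. This is a low-cost improvement to a secondary estimate and to one sentence of the Discussion.

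**What to change.** 1. Keep the observed prevalence. Beside it, report DR and STDR prevalence standardised to the baseline register of people with diabetes by age group and gender, and by duration if held for non-attenders, with standard errors clustered by FHC.
2. Use the standardised figure for the house-to-house comparison and for any statement of burden in the register. Keep observed prevalence times uptake for workload.
3. State that selection on unmeasured factors, such as visual symptoms, remains.
4. If register fields for non-attenders are not available, remove the selection-bias claim from the Discussion. In that case the planned uptake model would lack its covariates too, so this should be checked early.

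The cost is one further analysis, or one deleted sentence. Age- and gender-specific prevalence is already planned, and the uptake model already needs covariates on non-attenders. The drawbacks are somewhat wider intervals and correction only for characteristics that the register holds.
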